#### **Intervention B (es. comparison)**

The control group will follow the usual care practice of each Diabetes clinic including, at least, multi-language information material, pre-planned routine visits as recommended by National guidelines (SID, AMD 2021), and a cultural mediation intervention when required by the diabetologist.

#### **Adherence to intervention (addendum for operational protocol)**

The adherence to intervention and control will be monitored through clinical records and attendance registers fulfilled by the physician responsible for each phase of the intervention.

#### **Benefit-risk assessment for the population (addendum for operational protocol)**

Since the intervention and control group will undergo routinely proposed clinical and preventive interventions (i.e., routine visits and tests), no additional risks for the study participants are foreseen.

Benefits from the project and study results are foreseen at different levels, as described in the proposal.

The knowledge about how risk factors are acting in our Country on major chronic diseases in immigrants as well as the evidence about methods to contact hard-to-reach populations to propose preventive intervention and diabetes care can directly be used in planning tailored interventions for immigrant communities at particularly high risk of chronic diseases.

The results of the trial will pave the way to co-create interventions applicable to local communities of immigrants in any Italian context

The three levels of knowledge acquired with this project will be immediately transferable to three levels. First, the information on the current levels of integration of knowledge in the treatment process is relevant for planning purposes (implications for public health).

Second, the experience gained by the staff who will conduct the study will allow a direct transfer of knowledge in the local realities where the study is conducted with an important advancement in clinical practice (implications for clinical practice).

Third, the results of the clinical trial on culturally mediated interventions shared with migrant communities will allow a transfer of knowledge even at the level of elusive ethnic communities (implications for patient care).

#### **Participants' withdrawal (addendum for operational protocol)**

All the participants may withdraw from the study at any moment, and participation and compliance with follow-up will be monitored. Access to routine management will be guaranteed to each individual.

#### **Premature study termination or suspension (addendum for operational protocol)**

There are no anticipated stopping rules.

#### **Definition of study termination (addendum for operational protocol)**

For each participant, the study stops after participation in the 12-month routine visit.

#### **Study endpoints (addendum for operational protocol)**

##### **Primary endpoint**

The primary endpoint is the change in glycated haemoglobin (HbA1c; mmol/mol) between the recruitment and the 12-month follow-up visit assessed through the collection of fasting blood and urine samples.

The difference between groups of the mean change (and standard deviation) in glycated haemoglobin will be used to assess the effectiveness of the intervention.

##### **Secondary endpoint**

Secondary endpoints include:

- Biomarkers related to lipid profile assessed through the collection of fasting blood samples: triglycerides (mmol/l), LDL (mmol/l), HDL (mmol/l), total Cholesterol (mmol/l), free fatty acids (mmol/l), anthropometric measures (height, weight, BMI, waist circumference) and health related behaviours.
- Anthropometric measures: weight, height and waist circumference, bioelectrical impedance analysis (BIA).
- Systolic and diastolic blood pressure.
- Physical activity and dietary habits self-reported data.
- Increase in adherence to Mediterranean Diet

- restriction of daily alcohol consumption (<160 kcal);
- compliance with WHO recommended exercise goals
- Indicators of compliance with individual therapeutic protocols in terms of number of attended visits, number of tests of renal function and glycaemic control, and drug prescription.

Blood and urine samples and anthropometric measures will be collected at baseline and 12-month follow up visits.

Physical activity and dietary habits data will be collected through a questionnaire on lifestyle, dietary habit and physical activity fulfilled by each participant during routine visits in Diabetes clinics. The questionnaires used to assess dietary habits will be the Mediterranean Diet Score, (MedDietScore).(Panagiotakos 2007) The questionnaire used to assess physical activity will be the International Physical Activity Questionnaire - Short Form, IPAQ-SF. (Mannocci 2010)

Therapeutic adherence will be assessed at baseline and follow up visits using the Diabetes Mellitus Treatment Adherence Scale (DMTAS). (Hou 2021)

Descriptive analysis of mean (or median) changes with relative SD (or IQR) and the proportion of patients reaching therapeutic/recommended targets will be used.

## Study plan

### Study timeline (addendum for operational protocol)

The enrolment phase will last 4 months.

The intervention will last at least 3 months.

Questionnaires about diet and physical activity will be collected at baseline and 12-month visits, as well as anthropometric measures. The study timeline is reported in Figure 2.

Blood and urine samples will be collected at baseline and at 12 months to measure glycated haemoglobin and other biomarkers

[figure not shown]

Figure 2: Study timeline and data collection

### Sample size

To explore the efficacy of a culturally adapted diabetes education model in improving health literacy and self-care (primary endpoint) in immigrant patients with type 2 diabetes. The intervention is expected to provide a 0.5% higher reduction in the concentration of HbA1c compared to the usual care at a 12-month follow-up, with a positive effect on the risk of CVD events (Selvin 2004; Mitsios 2018). Through a change in health-related behaviours, it is also expected to reduce overweight and increase vegetable intake and physical activity, with a positive impact on future risk of non-communicable diseases and quality of life (GBD 2019 Risk Factors Collaborators 2020). To have a power of 80%, considering an alpha of 0.05 (Islam 2013), in order to detect a minimum significant reduction of 0.5% in the glycated haemoglobin in the intervention group compared to the control group at least 200 participants are needed (considering a SD in both group of 1.3) (Bellary 2008).

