### Study population (addendum for operational protocol)

The study will be performed within outpatients and inpatients' Diabetes clinics of the four Italian recruiting centres: Azienda Ospedaliero-Universitaria Careggi (Florence), Istituto Nazionale salute, Migrazioni e Povertà (INMP, Rome); Istituto in tecnologie avanzate e modelli assistenziali in oncologia-AUSL Reggio Emilia; Azienda Ospedaliero Universitaria Mater Domini (Catanzaro).

In each centre immigrants attending routine visits will be assessed for eligibility and, when appropriate, informed of the study and asked to participate. During the enrollment phase, cultural mediators will be involved if needed (subjects who do not speak or understand the Italian language will not be excluded). Due to the different ethnic compositions of the populations living in each centre, different minorities will be involved.

Intervention, control and follow-up will be performed within each centre.

According to the power analysis, at least 200 patients should be recruited overall.

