#### **Statistical plan**

Descriptive statistics will be calculated for baseline characteristics. The analysis will be intention-to-treat. Before/after variations of the glycated haemoglobin, lipid profile and renal function biomarkers, and anthropometric measure will be computed and standardized if opportune. Paired and unpaired tests will be used to assess the effects of the intervention and to analyse before/after within-group and between-group differences and changes in glycated haemoglobin. Changes in lifestyle habits (both related to diet and physical activities) will be described in terms of positive or negative changes.

Linear regression models will be used to analyse the variation of anthropometric measures and assessed biomarkers.

Multilevel linear models will be performed taking into account the influence of the centre on intervention efficacy.

We will perform a mediation analysis to understand which part of the changes in outcomes (glycated haemoglobin, lipid profile, and anthropometric measures) is attributable to changes in

physical activity, changes in diet, adherence to therapies, and other direct or unmeasured effects of the intervention.

The statistician will not be blinded to group assignments.

The statistical significance level will be set at 5%, and all analyses will be performed by using Stata 16 or SPSS 28.

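### The printed sample-size inputs need 214 analysed participants for 80% power (two-sided test assumed), not 200; no loss is allowed for, and the same paragraph mislabels the primary endpoint

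*Protocol*

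**What the plan says.** The Sample size section sets its targets with "To have a power of 80%, considering an alpha of 0.05". It takes a difference of 0.5% in HbA1c between the arms at 12 months as the effect to detect, and concludes that "at least 200 participants are needed (considering a SD in both group of 1.3" (the bracket goes on to cite a published trial). It does not state whether the test is one- or two-sided, whether 1.3 is the SD of HbA1c or of its change, or any allowance for loss to follow-up.

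The Study population section carries the same figure forward as the recruitment target: "According to the power analysis, at least 200 patients should be recruited overall". Intervention assignment gives a 1:1 ratio.

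On the analysis, the Statistical plan says "Paired and unpaired tests will be used to assess the effects of the intervention" and sets significance at 5%, again without sidedness. The Primary endpoint section compares the mean change in HbA1c between groups.

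On the endpoint itself, the Sample size section opens with a purpose of "improving health literacy and self-care (primary endpoint" (closing bracket omitted), while the endpoint section says "The primary endpoint is the change in glycated haemoglobin (HbA1c; mmol/mol" (likewise).

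**The concern.** A sample-size paragraph should let a reader recover the stated number from the stated inputs. Here the inputs lead to a larger number than the one printed. The number that the calculation says is needed is also the number to be recruited, although the endpoint requires a visit 12 months later and participants may withdraw at any time. If the trial gives a null result, it would be read as coming from a study with 80% power when the plan's own inputs do not give that.

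The endpoint label matters for another reason. The paragraph that justifies the trial's size attaches the words primary endpoint to a construct that is not the one being powered. The instruments listed under Secondary endpoint and Data collection (a Mediterranean diet score, a physical activity questionnaire and a treatment adherence scale) do not include a health-literacy measure.

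**Working it through.** **Inputs**

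- Difference 0.5, SD 1.3 in each arm, power 80%, alpha 0.05: Sample size section.
- Allocation 1:1, so 200 means 100 per arm: Intervention assignment and Study population.
- Unpaired comparison of mean changes: Primary endpoint and Statistical plan.
- Two-sided test: assumed. One-sided is also tried.
- Loss to follow-up: not given. 10%, 20% and 30% are used only as illustrations.

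**Step 1: try to reproduce 200**

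n per arm = 2 × (z for alpha + z for power)² × SD² / difference²

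- Two-sided: 2 × (1.96 + 0.8416)² × 1.3² / 0.5² = 106.1, so 107 per arm and **214** in total. By the noncentral t, 107 per arm falls just short (79.97%), so 108 per arm and **216** in total.
- One-sided: the same formula with 1.645 gives 83.6, so 84 per arm and 168 in total (85 per arm and 170 by the t-test).

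Neither gives 200.

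**Step 2: power at 200 analysed**

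Standard error = 1.3 × √(2/100) = 0.1838. Power = Φ(0.5/0.1838 − 1.96) = Φ(0.760) = **77.6%**; the noncentral t gives **77.2%**. The gap to 80% is 2.4 to 2.8 points, or 214 − 200 = 14 participants. One-sided power would be 85.9%.

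Two-sided 80% at 200 would need an SD of 0.5 / (2.8016 × √0.02) = 1.26, or a difference of 1.3 × 2.8016 × √0.02 = 0.515.

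**Step 3: loss before 12 months (assumed rates)**

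| Assumed loss | Analysed per arm | Power, two-sided (normal) | Power, two-sided (t) |
|---|---|---|---|
| 0% | 100 | 77.6% | 77.2% |
| 10% | 90 | 73.2% | 72.8% |
| 20% | 80 | 68.2% | 67.6% |
| 30% | 70 | 62.4% | 61.8% |

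**Step 4: why the kind of SD matters**

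The planned comparison is of changes. If 1.3 is the SD of HbA1c at each visit and r is the baseline-to-12-month correlation, the SD of the change is 1.3 × √(2(1 − r)). With assumed r:

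- r = 0.4: SD 1.42, power at 200 analysed 69.9%.
- r = 0.5: SD 1.30, power 77.6%.
- r = 0.6: SD 1.16, power 86.0%.

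So the stated power cannot be pinned down until the SD is defined.

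**Step 5: what baseline adjustment would do**

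If 1.3 is the SD of the 12-month value, adjusting for baseline reduces the working SD to 1.3 × √(1 − r²). At an assumed r = 0.5 this is 1.126, which gives 88.1% at 200 analysed and 80.2% at 160. At r = 0.25 it gives 80.2% at 200.

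**Step 6: the endpoint label**

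The Primary aim and the Primary endpoint section both name HbA1c change, and the calculation itself uses an HbA1c difference. Only the opening phrase of the Sample size section says otherwise.

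**The case against.** Several points against the concern have weight.

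- **Rounding.** The SD is printed to one decimal. An SD of 1.25 prints as 1.3 and gives 80.4% power at 100 per arm by the t-test, so 200 may have been right on an unrounded input. This stands as a reason not to call the design defective. It does not rescue the text: rounding can run the other way (an SD of 1.349 gives 74.2%), and a reader has only the printed 1.3.
- **Sidedness.** Two-sided is a convention here, not a stated input. On a one-sided 5% test, 200 analysed would exceed 80% power. That stands too, and is why the sidedness must be written down. One-sided alpha still does not yield 200 as the number needed, unless a loss allowance of about 15 to 16% is added that the protocol does not mention.
- **Attrition.** A reader might infer that the true power is likely somewhere between 62% and 77%. The protocol does not support that. It gives no loss rate, and both recruitment and the final assessment take place at routine diabetes visits. The lower figures are scenarios. What holds is the direction: with 200 as the recruited number, any loss reduces power.
- **Adjustment.** The Statistical plan includes linear regression and multilevel models, and a modest baseline correlation would restore 80% at 200. The Sample size section does not invoke this, however, and a correlation of 0.5 has no source in the protocol.
- **Endpoint and unit.** A reader might infer two rival primary endpoints. The aim, the endpoint section and the calculation all use HbA1c, so this is a stray label to correct. Nor does the use of % in one place and mmol/mol in another alter the sample size: the conversion is linear, so the ratio 0.5/1.3 is unchanged.

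**Conclusion.** The stated power does not follow from the printed inputs. Assuming a two-sided 5% test, 1:1 allocation and an unadjusted comparison with SD exactly 1.3, 80% power needs 214 analysed (216 by the t-test), and 200 analysed give about 77%. The arithmetic on the printed inputs is firm. The conclusion about the trial's actual power is less so, because sidedness, the kind of SD, the unrounded SD and the loss rate are all unstated. With complete follow-up the gap is modest; it grows with any loss, because 200 is the recruited number. The endpoint label is a plain contradiction that needs no calculation. Taken together, these should be fixed, but they do not show that the trial is too small to go ahead.

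**What to change.** In the protocol's Sample size section:

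1. Restate the power as about 77% for 200 analysed under the unadjusted two-sided comparison of changes, and note that 214 analysed (216 by the t-test) would be needed for 80%. State the sidedness.
2. Say whether 1.3 is the SD of HbA1c or of its change.
3. Give the expected analysed number, the loss rate assumed to reach it, and the power at that number. For example, 160 analysed, an assumed 20% loss, gives about 68%.
4. Alternatively to item 1, base the calculation on a baseline-adjusted analysis and name that analysis as primary so that the two match. If 1.3 is the SD of the 12-month value, an assumed correlation of 0.5 gives about 88% at 200 analysed and 80% at 160. The correlation must be labelled as assumed, preferably with a lower value shown beside it.
5. Replace the health literacy and self-care label with 12-month HbA1c change, to agree with the Primary aim and Primary endpoint sections.

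The cost is protocol wording, plus a slightly less favourable stated power unless the adjusted analysis is adopted. No extra patients are needed.

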### Screening of potentially eligible patients (addendum for operational protocol)

Physicians working at Diabetes clinics during routine visits will perform the eligibility assessment. Eligible patients will be informed on the study and asked to participate, collecting the informed consent.

### Recruitment process (addendum for operational protocol)

The recruitment will occur within Diabetes clinics routine visits in each centre.

Consecutive enrolment of potentially eligible patients will be performed over a four-month period. Whether low participation rates will occur, a preliminary eligibility assessment on medical records of Diabetes clinics will be performed, and potentially eligible patient will be actively contacted. Pre-recruitment eligibility criteria assessment from third sector organizations caring for undocumented migrants may also support active recruitment.

#### **Intervention assignment**

Block randomization (1:1 ratio) will be computerized and conducted in each centre to balance the ethnic composition of the intervention and control groups. Members of the same household, whether identified as cohabitant during the recruitment visit, will be assigned at the same arm.

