## **Study design**

The study is a multicentre randomized controlled open trial. The study design is reported in Figure 1.

Immigrants with type 2 diabetes registered at the Italian Regional Health Service or provided with STP code will be recruited.

Across the four recruiting centres, at least four different immigrant communities will be involved.

Endocrinology and Diabetology physicians at Diabetes clinics of both the National Health Service and non-governmental organizations (NGO) will do the recruitment.

Eligible immigrants who accept to participate will sign the consent during routine visits at Diabetes clinics and will be randomized to the control or intervention group.

The intervention group will receive a co-created culture-tailored intervention of health promotion aimed to increase healthy diet, physical activity and compliance with treatment protocols for diabetes.

The control group will receive the health promotion activities routinely performed by Diabetes clinics at the recruiting centres.

The enrolment phase will last 4 months.

The intervention will last at least 3 months.

Follow-up visits will be performed 12 months after recruitment.

The study period will be between 01/01/2023 and 31/12/2025, compatibly with the trend of the COVID-19 emergency.

Questionnaires about diet and physical activity will be collected at baseline and 12-month visits, as well as anthropometric measures.

Blood and urine samples will be collected at baseline and at 12 months to measure glycated haemoglobin and other biomarkers.

[figure not shown]

Figure 1. DiabEthic study design.

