### Eligibility criteria

#### Inclusion criteria

Eligibility criteria include:

- Immigrant status: Self-identification of being born in High migration pressure countries from parents born in High migration pressure countries (Carletti 2009);
- Age  $\geq 18$  years
- Type 2 diabetes newly diagnosed or with HbsA1c  $> 8\%$  in the last assessment within 24 months before the visit

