#### **Data processing and conservation (addendum for operational protocol)**

##### **Data collection**

The clinical information will be locally collected using the GDPR Compliant electronic platforms adopted by the recruiting centres for collecting clinical data allowing randomization.

Periodic monthly monitoring of recruitment, randomization procedures and follow-up will be collected on aggregated data reporting: number of patient contacted, refusal to participate (by sex and community), randomization (by gender, community and age group <50 and >50), presence at follow up visit.

Biomarkers will be assessed through analysis of blood and urine samples collected following standard procedures of the Diabetes clinics and analysed for glycaemia, by the authorised clinical laboratories of each recruiting centre.

Questionnaires used to assess dietary habits and physical activity will be the Mediterranean Diet Score, (MedDietScore) (Panagiotakos 2007) and the International Physical Activity Questionnaire - Short Form, IPAQ-SF. (Mannocci 2010)

Anthropometric measures will be collected following standard procedures during routine visits in Diabetes clinics with validated weight and height scales and bioelectrical impedance analysis (BIA). Therapeutic adherence will be assessed at baseline and follow up visits using the Diabetes Mellitus Treatment Adherence Scale (DMTAS). (Hou 2021)

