#### **Subgroup analysis**

Subgroup analyses will be performed according to weight status, gender, ethnicity, and socioeconomic level.

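### Blocks run by centre do not ensure the ethnic balance they are meant to give, because community is not a stratum within centre

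*Protocol*

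**What the plan says.** The Intervention assignment section gives one mechanism and one purpose: "Block randomization (1:1 ratio) will be computerized and conducted in each centre to balance the ethnic composition of the intervention and control groups". It names no stratum other than centre and gives no block size. It then adds a household rule: "Members of the same household, whether identified as cohabitant during the recruitment visit, will be assigned at the same arm".

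Other sections bear on whether centre can stand in for ethnicity:

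- Study population: "Due to the different ethnic compositions of the populations living in each centre, different minorities will be involved".
- Study design: "Across the four recruiting centres, at least four different immigrant communities will be involved". The number of communities per centre is not fixed.
- Inclusion criteria: the origin criterion is "Self-identification of being born in High migration pressure countries from parents born in High migration pressure countries", with no restriction to a named community at any centre. The Recruitment process section plans consecutive enrolment of those potentially eligible.
- Data collection: the monthly monitoring report tabulates "randomization (by gender, community and age group <50 and >50". Community is therefore known at allocation, but it is used there for reporting, not as a stratum.
- Subgroup analysis: "Subgroup analyses will be performed according to weight status, gender, ethnicity, and socioeconomic level".

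**The concern.** Permuted blocks within a centre hold the two arms close in size in that centre. They place no constraint on how the patients of any one community in that centre divide between the arms. If a centre enrols several communities, which the eligibility and recruitment text allows, the split within each community is left to chance. The sentence therefore credits the method with more than it secures.

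Ethnicity matters to this trial. The intervention is adapted to each community, ethnicity is a planned subgroup factor, and the Background reports that South Asian immigrants in Italy have more difficulty reaching glycaemic control. At stake are lopsided ethnicity subgroups, some loss of precision in the HbA1c contrast, and a reader's mistaken belief that ethnic balance was built in. The Statistical plan section names centre, but not community, as something its multilevel models account for.

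**Working it through.** The protocol gives no figure for ethnic balance, so there is none to reproduce. The check asks how uneven a community can become under the method as written.

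**Inputs from the protocol.** 1:1 blocks by centre; four centres; at least four communities; a total given as "at least 200 patients should be recruited overall".

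**Assumptions, not in the protocol.** 50 patients per centre (200 / 4), 25 per arm; communities of 8 or 10 within a centre; block size 4 and the ethnic mixes below for the simulation.

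**Step 1: one community within one centre.** With 25 per arm fixed, the number x of a community of size n in the intervention arm is hypergeometric:

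P(x) = C(25, x) × C(25, n − x) / C(50, n)

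- n = 10: P(5:5) = 53,130² / 10,272,278,170 = 0.275. P(6:4 either way) = 2 × 12,650 × 177,100 / 10,272,278,170 = 0.436. P(7:3 or worse) = 1 − 0.275 − 0.436 = 0.289.
- n = 8: P(4:4) = 12,650² / 536,878,650 = 0.298. P(5:3 either way) = 2 × 2,300 × 53,130 / 536,878,650 = 0.455. P(6:2 or worse) = 1 − 0.298 − 0.455 = 0.247.

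Simulating actual blocks of 4 gives nearly the same: 0.271 for 5:5, 0.289 for 7:3 or worse and 0.250 for 6:2 or worse. Block size hardly matters here.

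**Step 2: the whole trial.** Simulation of 4 centres × 50 patients, four communities, blocks of 4, 4,000 runs per cell. Each cell gives the chance that at least one community differs by 10 or more patients between arms, then the 95th percentile of the largest difference.

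| Assumed mix | Simple randomisation | Blocks by centre (as written) | Blocks by centre and community |
|---|---|---|---|
| One community per centre | 60.6%; 18 | 0%; 2 | 0%; 2 |
| 70/10/10/10, different main community in each centre | 54.0%; 18 | 18.7%; 12 | 0%; 4 |
| Four equal communities in every centre | 54.3%; 17 | 36.9%; 15 | 0%; 4 |

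Centre blocks help in every row, and fully so when each centre has one community. They leave a sizeable remainder when centres are mixed.

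**Step 3: effect on the primary contrast.** Take 100 per arm and let d be the difference in mean HbA1c change between one community and the rest, assumed to be 0.5 to 1.0 percentage points. The shift is the difference in the community's share between arms, times d.

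- 7:3 split: (0.07 − 0.03) × d = 0.02 to 0.04.
- 12-patient difference: 0.12 × d = 0.06 to 0.12.

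The Sample size section gives a target difference of 0.5 and an SD of 1.3, so the standard error is 1.3 × √(2/100) = 0.18. Both shifts are smaller than one standard error.

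**Step 4: effect on a subgroup of 10.** The standard error is proportional to √(1/a + 1/b). For 7:3 this is √(1/7 + 1/3) = 0.690; for 5:5 it is √(2/5) = 0.632. The ratio is 1.09, a loss of about 9%.

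None of these figures includes the household rule. Cohabitants sent to one arm depart from the block sequence, and where they share a community they make its split more uneven.

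**The case against.** The strongest reply is that the sentence is largely right. Ethnic mix differs by centre, so blocking by centre does serve ethnic balance. If each centre in practice recruits one main community, the purpose is largely met. The protocol neither states nor excludes this, and each centre does tailor the intervention to its own context. This stands in part: a reader might infer that centre blocks do nothing for ethnic balance, and the protocol does not support that. What remains is that balance within a mixed centre is not ensured. If every centre did have a single community, the ethnicity subgroups could not be told apart from centre.

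Second, a separate randomisation plan or SAP may name strata, and model covariates are usually settled there. That is possible. The point, however, is a property that the protocol itself attributes to the method it describes, not a missing detail.

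Third, a reader might infer that the HbA1c result would be biased. It would not: allocation remains random, the expected imbalance is zero, and Step 3 suggests a small shift in any one realisation. Covariate adjustment can deal with it, and monthly tabulation by community would at least reveal it.

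Fourth, a reader might take the Background to say that glycaemic control differs across all the ethnic groups. It says so only for South Asian immigrants; the group-by-group odds given there concern having diabetes. The protocol gives no difference between communities in HbA1c change, so the d used above is purely an assumption. A subgroup of 10 is uninformative at either split.

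**Conclusion.** The point holds in a limited form. Blocks by centre reduce ethnic imbalance but do not ensure balance between communities within a centre, because community is not a stratum and centres are not restricted to one community. With an assumed 50 patients in a centre, a community of 10 splits 7:3 or worse 29% of the time and one of 8 splits 6:2 or worse 25% of the time. Across the trial, the chance that some community differs by 10 or more patients runs from 0% to about 37% over the three assumed mixes.

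The consequence is chance imbalance. It bears mainly on the ethnicity subgroups and modestly on precision of the primary contrast. The size depends on centre sizes, community sizes and ethnic mix, none of which the protocol gives. The mismatch between purpose and method does not depend on them, unless every centre turns out to have a single community.

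**What to change.** 1. Stratify the computerised blocks within each centre by the main community or communities named for that centre, with all others pooled as 'other'. Vary the block size, since the trial is open.
2. State how cohabitants assigned to the same arm enter the sequence: whether they use up places in the block or are added outside it.
3. Include community, defined as in the strata, in the primary model alongside centre.
4. If the local platforms cannot stratify this way, reword the purpose as balance by centre, and keep the adjustment for community in the analysis.

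The cost is low. Randomisation is already computerised and community is already recorded for monitoring. The main downside is some incomplete blocks in small strata; with blocks of 4, an unfinished block leaves a difference of at most 2 in its stratum, and pooling rare communities limits how many there are. The protocol does not say what the local platforms can do, so this needs checking with each centre. The fallback needs one changed sentence and one added covariate.
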